#### Data collection and management responsibilities

Data collection will be the responsibility of the clinical trial staff at the site under the supervision of the site investigator. The investigator will be responsible for ensuring the accuracy, completeness, legibility, and timeliness of the data reported.

All source documents will be completed in a neat, legible manner (digital whenever possible) to ensure accurate interpretation of data. Clinical data (including concomitant medications, therapies, or other health-related aspects) will be entered into REDCap® (trial database), an electronic data capture system provided by the Department of Medical Informatics, Biometry and Epidemiology. The data system includes password protection and internal quality checks, such as automatic range checks, to identify data that appear inconsistent, incomplete, or inaccurate.

#### Study records retention

Anonymization, in the sense of deletion of personal data, takes place 10 years after the end of the study. Study documents will be retained for at least 10 years after the last publication. No records will be destroyed without the written consent of the principal investigator, if applicable.

### Data monitoring

#### Safety oversight

This is a multi-center study. Security is monitored centrally. There is a Data and Safety Monitoring Board (DSMB) that meets once a year and evaluates all AE and SAE reports. If there is an accumulation of study-related SAEs, the DSMB is convened early. The DSMB is composed of individuals with the appropriate expertise, including a biostatistician, pediatric pneumologists, and patient representative. Members of the DSMB will be independent from the study conduct and free of conflict of interest. The DSMB will provide its input to the financial sponsor of the study.

In addition to the DSMB, there is a study-independent “SAE board.” The members are specialists in the pediatric and internal medicine fields. This board evaluates events that led to a discontinuation of the intervention in the short-term for the study context and decides whether the intervention can be resumed without hesitation.

#### Clinical monitoring

Clinical site monitoring will be conducted to ensure that the rights and well-being of trial participants are protected; that the reported trial data are accurate, complete, and verifiable; and that the conduct of the trial is in compliance with the currently approved protocol/amendment(s), with International Council on Harmonisation Good Clinical Practice (ICH GCP), and with applicable regulatory requirement(s).

#### Quality assurance and quality control

Each clinical site will perform internal quality management of study conduct, data collection, documentation, and completion. All sites will follow a common quality management plan.

Quality control procedures will include:Informed consent

Study staff will review both the documentation of the consenting process as well as a percentage of the completed consent documents. This review will evaluate compliance with GCP, accuracy, and completeness. Feedback will be provided to the study team responsible for ensuring proper consenting procedures are followed.

b)Intervention fidelity

Consistent delivery of the study interventions will be monitored throughout the intervention phase of the study. Procedures for ensuring fidelity of intervention delivery are described in “Fidelity—interventionist training and tracking.”

c)Protocol deviations

The study team will review protocol deviations on an ongoing basis and will implement corrective actions when the quantity or nature of deviations is deemed to be at a level of concern.

This protocol defines a protocol deviation as any non-compliance with the clinical trial protocol or ICH GCP requirements. The non-compliance may be due to either the participant, the investigator, or the study site staff. In the event of non-compliance, corrective actions are developed and promptly implemented by the trial site. These practices are in accordance with ICH GCP. Non-compliance is defined as follows:Particularly noteworthy are gross violations of safety by the study centers or the intervention-carrying employees of the training institute [name]. [name], such as conducting study investigations without written consent for study participation.Refusal of the intervention is considered non-compliance for participants.

It will be the responsibility of the site investigator to use continuous vigilance to identify and report deviations within 7 working days of identification of the protocol deviation, or within 7 working days of the scheduled protocol-required activity. All deviations will be addressed in study source documents and reported to the Data Coordinating Center.

### Study discontinuation and closure

This study may be temporarily suspended or prematurely terminated if there is sufficient reasonable cause. Written notification, documenting the reason for study suspension or termination, will be provided by the suspending or terminating party to study participants, investigator, and funding agency. If the study is prematurely terminated or suspended, the principal investigator (PI) will promptly inform study participants, the EC, and sponsor/funding agency and will provide the reason(s) for the termination or suspension. Study participants will be contacted, as applicable, and be informed of changes to the study visit/assessment schedule.

Circumstances that may warrant termination or suspension include, but are not limited to:Determination of unexpected, significant, or unacceptable risk to participantsDevelopment of new evidence regarding the content of the study outside of the study during the study periodPoor recruitment

The study may resume once concerns about safety, protocol compliance, and data quality are addressed and satisfy the funding agency, EC, and steering committee.

## Discussion

This multi-center study is the first to investigate the effects of supported physical activity in pwPCD on quality of life. The evaluation of individual changes in quality of life in both the intervention and control groups and the stratification in the context of central randomization counteract possible biases due to the large age spectrum, center effects, and the very different disease severity. In addition, the analysis of individual changes in quality of life in combination with activity tracking also offers the possibility of classifying a possible increase in PA in the control group and its effects in the evaluation. In order to counteract frustration and thus an increased drop-out rate in the control group, the control group receives monthly reminder and email of thanks in addition to the activity tracking, as well as access to the online videos after the end of the study.

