**Methods:**

To test the main hypothesis, that an individualized and supported PA program leads to a better QoL 6 months after randomization (QoL-PCD questionnaire) compared to usual recommendation in pwPCD, 158 pwPCD aged 7 to 55 years are to be included in this multi-center randomized controlled trial (RCT). After the screening visit, a 1:1 randomization stratified by age group and FEV1 will be performed. A QoL-PCD questionnaire, motor test, and lung function will be carried out at regular intervals in both groups. PA is recorded in both groups using activity trackers during the study period. The main aim of the trial is to estimate the difference in the change of QoL between the groups after 6 months. Therefore, our full analysis set consists of all randomized patients and analysis is performed using the intention-to-treat principle. Statistical software R (http://www.r-project.org) is used. Ethical approvement without any reservations: RUB Bochum Ethics Committee (No. 23–7938; December 4, 2023). Recruitment start: March 2024.

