#### General procedure for recruitment via the patient organization

Recruitment as part of the patient congress

With the registration confirmation for the 2024 patient congress in Hamburg, the patient organization will send a reminder for the study. The inclusion and exclusion criteria are again pointed out here and congress participants are asked to bring all medical documents including cilia and genetic findings to the congress, if interested in study participation. This is necessary to be able to decide about eligibility for study participation at the congress. Congress participants who could take part in the study according to the inclusion and exclusion criteria will be informed verbally and in writing. After written information has been provided (see above), the screening visit including the motor test will be carried out on the same or following day. For the follow-up visits, appointments are either made at the lead study center in Bochum or the participants agree to a telephone visit. In this case, an examination close to home, including pulmonary function tests, is required by the treating doctor, for whom a confidentiality agreement must be in place. The following motor tests are carried out close to home after an appointment has been made with the training institute. The rest of the procedure corresponds to that in the study centers (see above).

b)Recruitment via mailing list or homepage

If a pwPCD contacts the central study center Bochum via advertising on the homepage or via the email distribution list of the patient organization, they will receive telephone and written information about the study. The inclusion and exclusion criteria will be checked in a telephone conversation. If participation in the study is not excluded in principle, an appointment will be made in Bochum for the screening visit and the motor test. Both will take part as described above for congress participants.

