#### Measures to minimize bias: randomization and blinding

To guarantee adequate sequence generation and allocation concealment, centralized online randomization with 1:1 allocation to intervention or control group is done through REDCap. A person at the AMIB not further involved in the study creates randomization lists based on permuted blocks of random length and are stratified by age group (6–12, 13–17, ≥ 18 years) and FEV1 (≤ / > 60%) to guarantee nearly equal group sizes within the strata. Allocation concealment will be ensured, as the service will not release the randomization code until the patient has been entered into the trial, which takes place after all baseline measurements have been completed.

It is not feasible nor possible for the participating patients and most project staff to be blinded to treatment allocation. Primary outcome assessment will be based on patient reports. Staff who analyze the data will be blinded (arms will be designated randomly at that point as A and B). Data review will be performed blinded.

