#### Analysis of the primary endpoint

The main aim of the trial is to estimate the difference in the change of quality of life between the intervention and control after 6 months in the domain of physical function. The confirmatory analysis will be conducted in the FAS based on the ITT principle. The analysis of the primary endpoint is carried out using a linear model. In addition to the intervention group, the model also includes baseline FEV1, gender and the interaction between age group, and baseline quality of life as independent variables. Estimated difference and corresponding two-sided confidence interval will be reported. In case of missing primary outcome, multiple imputation will be done. Missing values will be imputed from baseline and all available data after baseline.

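### The Discussion credits stratified randomisation with counteracting centre effects, but centre is neither a stratification factor nor a term in the models as described

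*Protocol article*

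**What the plan says.** The Discussion names two devices together. The first is looking at each participant's own change in quality of life. Of the second it says, taken with the first, that "the stratification in the context of central randomization counteract possible biases due to the large age spectrum, center effects, and the very different disease severity".

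The methods are narrower. The abstract says that "a 1:1 randomization stratified by age group and FEV1 will be performed". The section on randomisation and blinding describes lists that use "permuted blocks of random length and are stratified by age group" and FEV1, with three age bands and two FEV1 bands. Centre does not appear, although seven centres take part.

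For the primary analysis, besides the intervention group, "the model also includes baseline FEV1, gender and the interaction between age group, and baseline quality of life as independent variables". The secondary models for continuous outcomes list intervention group, gender, FEV1, age group and the baseline value of the outcome. Neither list contains centre. The section on statistical analyses calls this text an overview and leaves detail to an analysis plan that is not shown.

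Patients recruited at the congress may be followed at the lead centre or by telephone. In the telephone case "an examination close to home, including pulmonary function tests, is required by the treating doctor".

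**The concern.** A reader of the Discussion would credit the trial with a safeguard against centre effects that its randomisation does not contain. Of the three sources of bias named there, age and severity each correspond to a stratification factor. Centre corresponds to none.

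Two practical things follow. Within a centre the arms can be uneven by chance. Any difference between centres in outcome change also stays in the residual variance and widens the confidence interval. Lung function is the endpoint family most exposed, because a congress recruit's baseline and follow-up may be measured at different sites. The primary endpoint is a questionnaire completed on a tablet or through a link, so equipment does not affect it.

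**Working it through.** **1. Claim against methods.**

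| Source of bias named in the Discussion | Stratification factor | Term in the primary model |
|---|---|---|
| Age spectrum | Age group | Age group, in interaction with baseline QoL |
| Disease severity | FEV1, at or below / above 60% | Baseline FEV1 |
| Centre effects | None | None |

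The lists have 3 × 2 = 6 strata, and none is defined by centre. The abstract's own discussion paragraph makes a similar argument but names only the broad disease spectrum and the age range, so the main Discussion claims more than the abstract does.

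**2. Chance imbalance within a centre.** Inputs: 158 participants, seven centres plus one level for remote recruits. Average size: 158 / 8 = 19.75, about 20. Without centre strata, the number allocated to intervention in one centre is roughly Binomial(n, 0.5). The 2.5% to 97.5% range is 6 to 14 for n = 20 (30% to 70%) and 2 to 8 for n = 10. This describes balance within one centre. It does not measure error in the treatment estimate.

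**3. The plan's own sample size.** Effect size 15.2 / 30.4 = 0.5, two-sided t-test, 5% level. The exact calculation gives 63.8, so 64 per group, with 80.1% power at 64. The plan's 64 per group reproduces. Evaluable total: 2 × 64 = 128.

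**4. Power and type I error with and without centre.** Simulated trials of n = 128 had centres of unequal size, patient-level permuted blocks in six strata that ignore centre, a standard deviation of 30.4 and a true difference of 15.2 (0 for type I error). The share of outcome variance due to centre (ICC) is assumed, because the article gives none. One run used seven centres and fixed centre effects (5,000 trials per setting). The other used eight levels and a random intercept.

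| Assumed ICC | Power, no centre vs fixed effects | Power, no centre vs random intercept |
|---|---|---|
| 0 | 80.1% vs 78.2% | 79.4% vs 79.6% |
| 0.02 | 81.0% vs 79.9% | not run |
| 0.05 | 80.6% vs 80.3% | 80.9% vs 81.5% |
| 0.10 | 80.0% vs 81.7% | 79.7% vs 81.9% |
| 0.20 | 82.0% vs 86.9% | 81.5% vs 86.6% |

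Type I error without centre, over ICC 0 to 0.20, was 5.0% to 5.5% in the first run and 4.7% to 5.2% in the second. Monte Carlo error for a power near 80% with 5,000 trials is √(0.8 × 0.2 / 5,000) = 0.6 points, so differences below about one point should not be read closely.

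The random intercept gains 79.6 − 79.4 = 0.2 points at ICC 0, 81.5 − 80.9 = 0.6 at 0.05, 81.9 − 79.7 = 2.2 at 0.10 and 86.6 − 81.5 = 5.1 at 0.20. Fixed effects lose 80.1 − 78.2 = 1.9 points at ICC 0 and 81.0 − 79.9 = 1.1 at 0.02.

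**5. Ceiling in participants.** If a centre term removed all centre variance at no cost, it would be worth 128 / (1 − ICC) − 128 participants: 128 / 0.98 − 128 = 2.6 at 2%, and 128 / 0.90 − 128 = 14.2 at 10%. The simulated gain is the better guide, since centre effects must be estimated from few centres.

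**6. Stratifying by centre instead.** This would give 3 × 2 × 7 = 42 cells, with 158 / 42 = 3.8 participants each. Blocks would often stay incomplete, so this is not an attractive alternative.

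**The case against.** The strongest reply is that the sentence credits two devices jointly. Stratification could cover age and severity, while individual change covers centre. Change and baseline adjustment do remove stable differences in level between centres, and both models adjust for baseline. This answers part of the point. It does not cover centre differences in change, and the sentence as written still attaches stratification to centre effects.

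A second reply is that the analysis plan may add centre. That is possible, so the missing model term alone would not be a finding. It does not rescue the statement about stratification: recruitment began in March 2024, on lists described as using age and FEV1 only.

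A third reply is that little is at stake, and this stands. One training institute delivers the coaching in all centres, and standard therapy continues in both arms. Differences between centres in case mix, usual care or equipment are plausible but not documented. The ICC that matters is what remains after the baseline covariates, and it may be small.

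A reader might infer that centre effects are not handled at all, or that the treatment effect is biased. The article does not support either. Concealed, central, patient-level 1:1 allocation balances centre between arms in expectation, and the simulated type I error without centre stayed near 5%.

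**Conclusion.** The point holds as a misstatement with a modest cost in precision. Stratification by age group and FEV1 cannot counteract centre effects, and the models as described do not adjust for centre. The estimate remains unbiased.

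The price of leaving centre out is chance imbalance within centres and about 0 to 2 points of power at an ICC of 0 to 0.10, rising to about 5 points at 0.20. These figures rest on an assumed ICC, assumed centre sizes and 128 evaluable participants. Severity is minor. The sentence needs correcting whatever the analysis plan says; the model term is an inexpensive improvement.

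**What to change.** - **Wording.** In the Discussion, limit the stratification claim to age group and FEV1. For centre, rely on concealed patient-level randomisation and baseline adjustment.
- **Model.** Add centre as a random intercept, not as fixed effects, to the primary model and the continuous secondary models. Carry centre in the imputation model.
- **Definition.** Fix the centre level before randomisation: the recruiting or screening site, with one level for congress and mailing-list recruits. Do not define it by mode of follow-up, which may be settled after allocation. This single level absorbs an average shift only. It will not capture differences among local doctors' lung function measurements, and that should be stated as a limitation.

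The cost is analysis-plan wording and one extra variance parameter. If the centre variance is zero, no material power is lost (79.4% vs 79.6% in the simulation). The change should be made before unblinding. Randomisation stays as it is.

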## Trial status

Recruitment started on March 5, 2024, and is expected to end on March 31, 2025. The period from first patient in to last patient out is planned to be 24 months. The trial is based on the study protocol version 1.1 dated November 10, 2023. The protocol was updated in June 2024 (version 1.2).

## Data Availability

The datasets analyzed during the current study and statistical code are available from the corresponding author on reasonable request, as is the full protocol. Data access request will be reviewed by the study team. Data will not be published on open data repository due to the inclusion of children and adolescents with a heterogeneous rare disease with a high risk of re-identification.

## Abbreviations

AE: Adverse event
CF: Cystic fibrosis
CONSORT: Consolidated Standards of Reporting Trials
COPD: Chronic obstructive pulmonary disease
CRF: Case report form
DCC: Data Coordinating Center
DSMB: Data Safety Monitoring Board
EC: Ethics committee
eCRF: Electronic case report form
ERS: European Respiratory Society
FAS: Full analysis plan
FEV1: Forced expiratory volume in 1 s
FVC: Forced vital capacity
GCP: Good Clinical Practice
ICD: Implantable cardioverter defibrillator
ICH: International Council on Harmonisation
ITT: Intention-to-treat
LCI: Lung Clearance Index
MEF 75/25: Maximum expiratory flow at 75/25% of FVC
NIV: Non-invasive ventilation
OHRH: Office for Human Research Protections
PA: Physical activity
PCD: Primary ciliary dyskinesia
PEF: Maximum expiratory flow or peak flow
PI: Principal investigator
PPS: Per protocol set
PTCA: Percutaneous transluminal coronary angioplasty
pwPCD: Persons with PCD
QoL: Quality of life
RCT: Randomized controlled trial
SAE: Serious adverse event
SAP: Statistical analysis plan
sReff: Specific airway resistance
TLC: Total lung capacity
VCmax: Maximum vital capacity
V0–4: Screening and study visits
